### Safety

During the 6-week therapy/intervention phase, participants will have the opportunity to contact a corresponding outpatient clinic in a nearby city by telephone (lists with opening hours, web-links, postal addresses, and telephone numbers will constantly be provided in the corresponding language). In addition, a medical advisory and emergency list in case of an emergency will be provided according to the web-based treatment guidelines from the Federation of Swiss Psychologists [25] (in line with the HONcode [26], a code of ethics for medical information on the Internet). This list will always be accessible before, during, and after (pdf-version for print out) the study participation regardless of whether they withdraw or drop out of the study. This list will include numbers of emergency help lines and the contact information of the study team and the webmaster.

### Trial Flow

Figure 1 provides an overview of the trial flow. If a participant successfully completes the baseline assessment (t0), he or she will be introduced step-by-step into either the intervention or the control tool (part 1) and invited to participate in module 1. Every week and two days in advance to the next module, a participant will receive an automated e-mail notification to login and return to the next module. Modules 1 to 4 will be accessible only week by week. After three weeks, the automated e-mail will direct the participant to the intermediate assessment (t1) before he or she has access to module 4 of the intervention or the control tool (end of part 2). Six weeks after the baseline assessment, completion of the additional optional modules of part 3 and weekly reminder e-mail notifications, participants will be invited again by e-mail to login and complete the final study assessment (t2). It is possible that some participants will wish to continue with some of the modules in part 3 after this period. However, the decision has been made to have the follow up timing depend solely on the time interval since t0. In our opinion, this is the best possible adherence to the 'intention to treat' principle. For the follow up assessment (t3), participants will be invited by an e-mail message 6 months past t0, with the notification that completion of the entire 6-month follow up assessment will be compensated by a 40 Euro incentive (an online voucher or an online charitable donation).

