### Hypotheses

We hypothesise that Snow Control participants in the therapy group will show higher reductions on the Severity of Dependence Scale (SDS) [20] sum score and cocaine consumption than those in the control group at the 6-week treatment termination and at the 6-month follow up. Moreover, we expect participants in the therapy group to improve more significantly with respect to the secondary outcomes between baseline and 6-week treatment termination. We also expect the participants in the therapy group to show significantly higher retention.

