### Randomisation and Allocation

Once participants have completed their baseline assessment, they will be randomly brought to part 1 of either the intervention or the control tool, and this assignment will be automatically registered in the background database. This assignment will also be registered in their Internet browser as a cookie to avoid multiple registrations by one person. If a person returns to the Snow Control start page and attempts to register for a second time, she or he will be recognised by the background database and automatically be redirected to his or her allocation.

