### Handling of study dropouts

Each week, participants will be sent an automated e-mail that contains a reminder to work on the next module and a direct link to the Snow Control login site. If participants do not log in, they will receive a reminder e-mail every three days within the following two weeks. If they do not continue their participation after these reminders, they will be considered to have dropped out of the study. Participants who skip one of the study questionnaires by not answering all of the questions will be identified in the data analyses and counted as dropout (cut-off: answered at least 70% of the questions).

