### Data Analysis

Data will be analysed according to the intention-to-treat principle. Multiple imputations of missing data handling procedures will be implemented using the statistical software package STATA (version 10). Baseline measurements will be compared using t- and Chi-squared tests. Differences between primary and secondary outcome variables at three and six weeks will be tested using a repeated measures ANOVA. Effect sizes will be calculated using Cohen's d [27]. Differences in treatment retention will be tested using multiple logistic regression analyses. We will additionally conduct explorative regression analyses in order to test whether baseline variables predict cocaine abstinence, cocaine craving (CCQ-B), or reduced symptoms of depression (BDI-V). For these analyses, we will use linear, multinomial, or binary regression models dependent on the scale level of the outcome measures.

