During the online implementation of the consumption diary of the Snow Control therapy group, we considered asking pilot participants to note the number of cocaine lines consumed. The pilot tests showed that although this includes some numeracy skills, pilot participants did not feel disturbed to note their consumption in grams of cocaine consumed per day. However, because the well-established SDS is utilised as the main outcome and the CCQ-B as a secondary instrument with a randomised control group, we do not expect much influence of purity and quality of the cocaine consumed or the methods of consumption to interfere with the potential outcome differences.

Finally, a potential problem for this trial is the expected high number of lost participants at the end of and at follow up of the online therapy, which will likely be even higher in the control intervention. We will address this issue in three ways. 1) All participants must invest approximately 30 minutes for the baseline assessment, which will select rather motivated participants and prevent the participation of un-motivated participants. 2) Participation at 6 months follow up assessment will be compensated by a 40 Euro incentive (an online voucher or an online charitable donation). 3) All missing values in the final data set will be multiple-imputed, a promising approach that, as shown by our Dutch colleagues, has become increasingly important in e-health research [34].

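### The 6-week assessment carries a main hypothesis and 70% expected loss, yet has the least collection support; completion-triggered reminders and a gate would help at little cost

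*Protocol article*

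**What the plan says.** The article sets a different collection rule for each assessment.

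- **Baseline (t0)** comes before allocation: "Once participants have completed their baseline assessment, they will be randomly brought to part 1 of either the intervention or the control tool" (Randomisation and Allocation).
- **3 weeks (t1):** "the automated e-mail will direct the participant to the intermediate assessment (t1) before he or she has access to module 4" (Trial Flow).
- **6 weeks (t2):** after a period of weekly reminder e-mails, "participants will be invited again by e-mail to login and complete the final study assessment (t2") (Trial Flow). No gate and no payment are stated.
- **6 months (t3):** also by e-mail, with the notice that "completion of the entire 6-month follow up assessment will be compensated by a 40 Euro incentive" (Trial Flow).

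Under Handling of study dropouts, the weekly e-mail prompts work on the next module. "If participants do not log in, they will receive a reminder e-mail every three days within the following two weeks"; anyone who still does not return is then counted as a dropout.

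The Hypotheses section expects larger reductions in the Severity of Dependence Scale (SDS) and in cocaine use in the therapy arm "than those in the control group at the 6-week treatment termination and at the 6-month follow up". Data Analysis states: "Differences between primary and secondary outcome variables at three and six weeks will be tested using a repeated measures ANOVA", under intention to treat with multiple imputation. The sample-size section expects 70% to leave before completing six weeks.

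**The concern.** Week 6 is a hypothesised endpoint, is in the only outcome test the article names, and is the one time point with a quantified loss. It is also the post-baseline assessment with neither a gate nor a payment. The stated reminders respond to absence from the website, not to an unanswered questionnaire, so the people easiest to reach, those still logging in, can be missed.

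At stake is how much of the 6-week result is observed and how much is imputed. The Discussion also expects loss to be higher in control, so what is imputed would differ in amount between arms.

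**Working it through.** **1. The plan's own figure.** Inputs from the sample-size section: 25 per group, 70% loss by six weeks, 170 recruited.

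- 2 × 25 / (1 − 0.70) = 166.7, so 167. The stated 170 is reproduced to within 2%.
- Expected observed at week 6: 170 × 0.30 = 51. Expected missing: 170 − 51 = 119.

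**2. Collection rules side by side.**

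| | t1 (3 weeks) | t2 (6 weeks) | t3 (6 months) |
|---|---|---|---|
| Gate | before module 4 | none stated | none stated |
| Payment | none stated | none stated | 40 Euro |
| Named in main hypothesis | no | yes | yes |
| Named in the ANOVA | yes | yes | no |

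**3. A case the rules do not catch.** Trial Flow foresees that some participants will continue part 3 modules after week 6. Suppose one logs in on day 43, works on a module and does not open t2. The reminder rule is not triggered, because the person logged in. Nothing stated requires t2 before the module. Apart from the invitation itself, no stated rule prompts for the missing questionnaire.

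**4. The Discussion's three measures, tested against week 6.** They are offered for loss both at the end of therapy and at follow-up.

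- The baseline of about 30 minutes acts before randomisation.
- The payment is for the later time point: "Participation at 6 months follow up assessment will be compensated by a 40 Euro incentive".
- Multiple imputation acts after the data are lost.

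None is a post-randomisation collection measure for week 6.

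**5. What more observed data would be worth.** The response gains here are assumptions; the article gives none. The calculation is for completers only, with equal arms of n = 170r/2 at response r, a difference of 3.75 points and two-sided α = .05. Power = Φ(3.75 / (SD × √(2/n)) − 1.96). The SDs of 7.5 and 5 are the plan's.

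| Response r | Observed | SE relative to r = 30% | Power, SD 7.5 | Power, SD 5 |
|---|---|---|---|---|
| 30% | 51 | 1 | 0.431 | 0.764 |
| 40% | 68 | √(51/68) = 0.866 | 0.540 | 0.871 |
| 50% | 85 | √(51/85) = 0.775 | 0.635 | 0.933 |

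The power at 30% is below the stated 0.8 because 25 per group does not follow from a two-group formula with these inputs (SD 7.5 gives 63 per group, two-sided). That is a separate matter.

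**6. Does uneven collection bias the comparison of arms?** Take an assumed normal selection model with SD 7.5 and correlation ρ between outcome and response. The bias among completers has size ρ × 7.5 × [λ(control retention) − λ(therapy retention)], where λ(p) = φ(z₁₋ₚ)/p.

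- 30% in both arms: 0 for every ρ.
- 35% against 25%: λ = 1.058 and 1.271, so 0.16 points at ρ = 0.1 and 0.80 at ρ = 0.5.
- 40% against 20%: 0.33 to 1.63 points over the same range.

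Bias comes from retention or selection that differs by arm, not from a rule that differs by time but is common to both arms.

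**The case against.** The strongest reply is that the trial compares arms, that each rule is the same in both, and that imputation is planned. This stands. A reader might infer that changes from 3 to 6 weeks, or from 6 weeks to 6 months, merely reflect who answered. The documents do not support that: the analysis is not one of successive responder sets, and the named ANOVA leaves out the paid 6-month point.

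A reader might also infer that week 6 will have the poorest response of all. That cannot be shown. No response rate is given for 3 weeks or 6 months, the Discussion expects high loss at follow-up too, and the 3-week gate binds only people who still want module 4. Nor is week 6 without reminders: weekly e-mails precede it, and failure to log in after the invitation may well fall under the three-day rule, though that rule is worded for modules.

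Two further points stand. The 70% are people who quit the study, not active users who skip t2. A gate reaches only those who log in from day 42, possibly few, so the 40% and 50% rows above are not forecasts for it. And a condensed article may leave website routing to a fuller document. But this article does state its gate, payment and reminder trigger, and the point rests on those stated rules.

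**Conclusion.** The point holds as a low-cost improvement to stated collection rules, not as a demonstrated bias. Of the post-baseline assessments, week 6 is the least supported, and none of the Discussion's measures helps to collect it after randomisation. The consequence is about 51 observed 6-week outcomes out of 170 if the plan's 70% loss is right, so about 70% of that endpoint rests on imputation.

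Uneven rules over time do not themselves bias the contrast between arms. The expected excess loss in control could: in the illustration, retention of 35% against 25% gives about 0.2 to 0.8 SDS points, against the planned 3.75. That range rests on an assumed selection model and applies to completers, not to the imputed analysis. More observed data would lessen the reliance on imputation, but how much more can be obtained is not known.

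**What to change.** In both arms:

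1. Trigger the three-day reminders for t1, t2 and t3 by the assessment not being completed. Send them to every randomised participant who has not withdrawn consent, whether or not the modules are still in use.
2. From day 42, open t2 at the first log-in, before any further part 3 module, as is already done with t1 before module 4.

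Leave the 40 Euro at 6 months. Moving part of it to week 6 would weaken collection at another hypothesised endpoint.

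The cost is a small change to website routing and mail triggers, some extra e-mails, and a questionnaire in the way of participants who want another module after week 6. No incentive money is needed.

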**Figure 1 F1:**
[figure not shown]
**Trial flowchart. This figure provides an overview of the participant flow for this trial**.

### Handling of study dropouts

Each week, participants will be sent an automated e-mail that contains a reminder to work on the next module and a direct link to the Snow Control login site. If participants do not log in, they will receive a reminder e-mail every three days within the following two weeks. If they do not continue their participation after these reminders, they will be considered to have dropped out of the study. Participants who skip one of the study questionnaires by not answering all of the questions will be identified in the data analyses and counted as dropout (cut-off: answered at least 70% of the questions).

### Data Analysis

Data will be analysed according to the intention-to-treat principle. Multiple imputations of missing data handling procedures will be implemented using the statistical software package STATA (version 10). Baseline measurements will be compared using t- and Chi-squared tests. Differences between primary and secondary outcome variables at three and six weeks will be tested using a repeated measures ANOVA. Effect sizes will be calculated using Cohen's d [27]. Differences in treatment retention will be tested using multiple logistic regression analyses. We will additionally conduct explorative regression analyses in order to test whether baseline variables predict cocaine abstinence, cocaine craving (CCQ-B), or reduced symptoms of depression (BDI-V). For these analyses, we will use linear, multinomial, or binary regression models dependent on the scale level of the outcome measures.

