## Methods/Design

### Aims of the trial

This study aims to test the effectiveness of the web-based cognitive-behavioural self-help therapy Snow Control to reduce cocaine use in problematic cocaine users in a two-arm randomised controlled trial. The primary outcome is the change in severity of cocaine dependence between baseline, 3 and 6 weeks of therapy/intervention and at a 6-month follow up. The secondary outcome measures include changes in cocaine craving, the past month's consumption of cocaine and other substances of abuse and changes in depression characteristics. The predictive validity of participant characteristics for treatment retention and outcome will be explored.

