### Estimation of the Expected Effect Sizes and Sample Size

The maximal SDS score is 15 points, and the average SDS standard deviation in previous studies was 5 points. As we expect relatively large cocaine consumption differences between participants, we expect a conservative SDS deviation of 7.5 points. For a successful reduction in cocaine use, an average 25% SDS score reduction (3.75 points reduction for a small to medium effect size) is anticipated. This results in a total sample of 25 participants in each group (α = .05, 1-β = 0.8). According to the pilot study, we expect 70% of the participants to quit the study before completion at six weeks. We thus aim to recruit a total of 170 participants at baseline.

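### The planned repeated measures ANOVA does not isolate the hypothesised 6-week SDS difference, no test is named for the 6-month hypothesis, and a baseline-adjusted contrast would answer both at the cost of wording

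*Protocol article*

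**What the plan says.** The confirmatory method is one sentence in Data Analysis: differences in the primary and secondary outcomes "at three and six weeks will be tested using a repeated measures ANOVA". It names no covariate, no contrast, and no term of the ANOVA as the test.

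The Hypotheses section expects larger SDS reductions in the therapy group "than those in the control group at the 6-week treatment termination and at the 6-month follow up". Week 3 is not a hypothesised time point for SDS. Aims of the trial defines the outcome over all four assessments: "The primary outcome is the change in severity of cocaine dependence between baseline, 3 and 6 weeks of therapy/intervention and at a 6-month follow up".

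SDS is measured at baseline, 3 weeks, 6 weeks and 6 months (Table 2), and the baseline value precedes allocation: "Once participants have completed their baseline assessment, they will be randomly brought to part 1". The only use of baseline values that Data Analysis states for the arm comparison is a check of balance: "Baseline measurements will be compared using t- and Chi-squared tests". Missing data are to be multiply imputed under intention to treat.

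**The concern.** The hypothesis concerns a difference between arms at two particular times. The named test covers two visits, of which only one is hypothesised for SDS, and omits the other hypothesised time altogether. A significant result would not by itself show that SDS fell further at 6 weeks. The group effect over weeks 3 and 6 could be carried mainly by week 3. A group-by-time result does not say at which visit, or in which direction, the arms differ. Because the tested term is not named, it could also be chosen after the data are seen.

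The second issue is efficiency. The baseline score is available for every randomised participant. With about 25 completers expected per arm, the choice between an omnibus test and a baseline-adjusted contrast can change power noticeably.

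**Working it through.** **The plan's own figure.** The effect is taken from "an average 25% SDS score reduction (3.75 points reduction for a small to medium effect size) is anticipated" and the spread from "we expect a conservative SDS deviation of 7.5 points", so d = 3.75/7.5 = 0.5, read as a between-arm difference at 6 weeks. For two arms, two-sided α = 0.05 and 80% power:

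n = 2 × [(1.960 + 0.842)/0.5]² = 62.8, i.e. 63 per arm (50 if one-sided).

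The stated 25 per group is not reproduced. Only a one-sample, one-sided calculation at d = 0.5 returns 25. From 25 per group the recruitment target does follow: 50/(1 − 0.7) = 167, rounded to 170.

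**Inputs for the comparison.** n = 25 complete per arm and d = 0.5 at week 6 come from the sample-size section. Two inputs are assumptions, because the article gives neither: the correlation ρ between visits (equal for all pairs, 0.3 to 0.7) and the week-3 effect (half the week-6 effect, or equal to it).

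**Formulas** (two-sided 5%, noncentral t or F):
- Unadjusted week 6: ncp = d/√(2/n) = 0.5/0.283 = 1.77; power 41%.
- Week 6 adjusted for baseline: ncp = d/√[2(1 − ρ²)/n], 47 df. At ρ = 0.5: 0.5/√(2 × 0.75/25) = 2.04.
- Average of weeks 3 and 6: mean effect/√[2 × ((1 + ρ)/2)/n], 48 df. At ρ = 0.5: 0.375/0.245 = 1.53 (half) or 0.5/0.245 = 2.04 (equal).
- Group-by-time over weeks 0, 3 and 6: λ = (n/2) Σ(δₜ − δ̄)²/(1 − ρ), 2 and 96 df. At ρ = 0.5: effects 0, 0.25, 0.5 give 12.5 × 0.125/0.5 = 3.13; effects 0, 0.5, 0.5 give 12.5 × 0.1667/0.5 = 4.17.

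**Power, 25 per arm**

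| Test | ρ = 0.3 | ρ = 0.5 | ρ = 0.7 |
|---|---|---|---|
| Week 6, adjusted for baseline | 44% | 52% | 68% |
| Group-by-time, week-3 effect half | 24% | 32% | 51% |
| Group-by-time, week-3 effect equal | 31% | 42% | 64% |
| Average of weeks 3 and 6, half | 36% | 32% | 29% |
| Average of weeks 3 and 6, equal | 58% | 52% | 47% |

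The formula slightly flatters the adjusted contrast, because it leaves out chance imbalance in baseline. Simulation puts that row at about 43%, 50 to 51% and 67%. The gain over group-by-time is then about 3 to 19 points (4 to 20 by formula).

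**Does adjustment rescue the sample size?** The adjusted test needs 62.8 × (1 − ρ²) per arm: 58 at ρ = 0.3, 48 at 0.5, 33 at 0.7. For 25 to suffice, ρ = √(1 − 25/62.8) = 0.78.

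**The case against.** The strongest reply is that the article is silent on covariates and contrasts; it does not rule them out, and such detail commonly sits in a fuller document. That is fair as to the covariate. It does not explain why the one sentence that fixes the time points names weeks 3 and 6 when the hypotheses name 6 weeks and 6 months.

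A reader might infer that the ANOVA ignores baseline. The text does not support this as a general statement. The outcome is defined as change from baseline, so baseline may well be a level of the time factor, with group-by-time as the test. On that reading baseline is used, only less efficiently.

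A reader might also object that a classical repeated measures ANOVA needs complete rows when 70% loss is expected. The planned multiple imputation, stated in Data Analysis and repeated in the Discussion, answers this. The same plan limits the calculation above: 25 complete rows per arm is not the planned analysis set, and power after imputation cannot be derived from the article.

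The power argument also depends on the week-3 effect. Three of the four key modules open before the 3-week assessment, so a full early effect cannot be excluded. In that case the week 3 and 6 average ties with the adjusted contrast at ρ = 0.5 and beats it at ρ = 0.3.

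Finally, significance tests on baseline values are a common reporting habit, and nothing in the article makes later adjustment depend on them. They add little, since random allocation already makes any difference a chance one, but they do not show data-driven adjustment.

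**Conclusion.** The point holds as a mismatch between hypothesis and test, together with an efficiency gain that costs nothing in data. The mismatch needs no assumption: the stated ANOVA does not isolate the 6-week SDS difference on either plausible reading, and no test is named for SDS at 6 months.

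The efficiency part is conditional. If the test is group-by-time with baseline as a level, the adjusted 6-week contrast was more powerful in every setting examined, by about 3 to 19 points for correlations of 0.3 to 0.7. At correlation 0.5 the comparison is about 32% against 50% with a half-size week-3 effect, and 42% against 51% with an equal one. If the test is the average of weeks 3 and 6, the gain can vanish or reverse when the effect is full by week 3 and the correlation is 0.5 or lower. The case against that average is then that it aims at the wrong quantity, not that it loses power. These figures rest on compound symmetry, complete data in 25 per arm, and an assumed correlation and week-3 effect.

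It would be wrong to conclude that baseline adjustment secures the stated 80% power. At 25 per group and a standard deviation of 7.5, that would take a correlation of about 0.78, for which the article gives no support.

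**What to change.** Name one primary test: the between-arm difference in SDS at 6 weeks, adjusted for baseline SDS, reported in points with a 95% CI. Either of two forms would serve: ANCOVA on each imputed data set, pooled by Rubin's rules, or a mixed model of post-baseline SDS with arm, visit, arm-by-visit and baseline SDS, from which the 6-week contrast is taken. Add the same baseline-adjusted contrast at 6 months, so that the second half of the hypothesis has a test. Report baseline characteristics by arm descriptively in place of the t- and Chi-squared tests. State the correlation assumed in any revised power statement.

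The cost is analysis wording only: SDS is already scheduled at all four assessments, and no visit, instrument or participant is added. The sample-size justification needs separate correction.
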